### Endpoints

#### Primary endpoint measures

The primary endpoint measures will be the percentage of patients receiving pain relief at T1, T2, and T3. Repeated-measures analysis of variance will be used for data analysis.

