### Treatments

Eligible patients will receive oral immediate-release morphine with a proportion of 10–20% daily total doses of oral morphine as the standard breakthrough pain treatment [24]. Patients will be instructed to use of study apparatus, which provides a fix concentration of nitrous oxide/oxygen mixture or oxygen to a disposable, demand valve, scented oral–nasal mask. Patients will hold the mask, which is opened by the negative pressure of patients to control the gas taken in. The experimental group will receive a fixed concentration of nitrous oxide/oxygen mixture and the control group will receive oxygen during breakthrough pain episodes. Gas inhalation will be administered until the breakthrough pain episode is over. The project manager is in charge of assignment, allocation, and treatment delivery. All gas cylinders used in both two groups are identical in appearance. The patients, nurse, and data collector are all blind to the treatment.

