### Sample size determination

According to our previous study on burn-dressing pain [17, 37], we used preliminary observational data obtained in medical oncology for 20 patients. We found that 90% of patients receiving pre-prepared nitrous oxide/oxygen mixture experienced pain relief (a decrease of at least 30% in pain intensity [47]) at 15 min versus 10% of patients in the control group. The aim of this study is to assess the efficacy of the nitrous oxide/oxygen mixture, so a sample size of 12 was targeted with a two-tail test with type-1 error rate of 0.05 and a power of 90% to be sufficient. We decided on a sample size of 240 to meet the Chinese Food and Drug Administration standard for feasibility and the safety of nursing staff in implementing this analgesic [17].

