### Data management and analysis

Before the study, all data collectors will be trained in the data collection procedure. Data from withdrawn patients will not be used in the final analysis. SPSS version 22.0 (SPSS Inc., IBM Company, Chicago, IL, USA) will be used to conduct quantitative analysis following the intention-to-treat principle for a case-control randomized trial. Descriptive statistics will be analyzed by medians (inter-quartile ranges), means (standard deviations), and proportions (exact binomial 95% confidence intervals), as appropriate. Proportions will be compared by using the chi squared test or the Fisher’s exact test. Means will be compared using Student’s *t* test (normal distribution parameters) or a nonparametric two-sample Mann–Whitney test (non-normal distribution parameters). Statistical significance will be considered for *P* < 0.05.

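### The yes/no primary endpoint is assigned repeated-measures ANOVA in one section and chi-squared or Fisher's test in another, so the primary test is ill-matched to the endpoint and not unique

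*Protocol article*

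**What the plan says.** Three sections of the protocol article bear on the primary analysis.

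- **Primary endpoint measures** defines the endpoint: "The primary endpoint measures will be the percentage of patients receiving pain relief at T1, T2, and T3". The next sentence gives the method: "Repeated-measures analysis of variance will be used for data analysis". It does not name the deciding ANOVA term (group, time or group by time).
- **Sample size determination** defines relief as "a decrease of at least 30% in pain intensity", so each patient scores yes or no at each time. The planning rates are for 15 min, which is T2: "90% of patients receiving pre-prepared nitrous oxide/oxygen mixture experienced pain relief" "at 15 min versus 10% of patients in the control group".
- **Data management and analysis** says "Proportions will be compared by using the chi squared test or the Fisher’s exact test". It does not mention repeated-measures ANOVA. It sets P < 0.05 with no rule for combining three times.

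The randomization section puts 180 patients in A, B and C together and 60 in D. All of A, B and C receive the mixture, and the Treatments section speaks of two groups ("All gas cylinders used in both two groups are identical in appearance"), so the natural comparison is A+B+C pooled versus D.

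**The concern.** Repeated-measures ANOVA assumes continuous responses with the same covariance matrix in each group. A yes/no response has variance p(1−p), so the arms' variances differ whenever their relief rates are not equally far from 50%. With 3:1 allocation, unequal variances distort any F test that pools them.

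Separately, two sections assign different tests to the same proportions, and the sample size follows the one not named beside the endpoint. The confirmatory P value could then depend on which test, which ANOVA term or which time is reported.

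**Working it through.** **1. Which test does the sample size rest on?** Inputs from Sample size determination: 90% versus 10%, two-sided 0.05, power 90%, total 12. The uncorrected two-proportion formula at 1:1, with mean rate 0.5, gives

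n per arm = [1.960·√(2·0.5·0.5) + 1.282·√(0.09 + 0.09)]² / 0.80² = (1.386 + 0.544)² / 0.64 ≈ 5.8, so 6 per arm and 12 in total.

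The stated 12 is reproduced (exact chi-squared power with 6 per arm: 90.5%). The sizing therefore matches a two-proportion test at T2, not an ANOVA over three times.

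**2. ANOVA with identical arms.** Correlated yes/no data at three times were simulated, 180 versus 60 patients, with the same rates in both arms. Across the assumed rates and correlations, the group main effect rejected 4.4% to 5.6% and group by time 4.8% to 5.9%. Both are close to the nominal 5%.

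**3. Group by time when the arms differ by a constant amount.** The true interaction on the risk-difference scale is zero, so rejection should be 5%. Let v = p(1−p), with T for A+B+C and D for control. Assuming equal within-patient correlation in both arms:

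- true variance of the contrast ∝ v_D/60 + v_T/180 = (3v_D + v_T)/180
- variance used by the F test ∝ [(60v_D + 180v_T)/240]·(1/60 + 1/180) = (v_D + 3v_T)/180
- ratio R = (3v_D + v_T)/(v_D + 3v_T)
- large-sample rejection (2 degrees of freedom) ≈ 0.05^(1/R)

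The simulated column comes from repeated runs with latent correlation 0.5.

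| Relief T/D (%) | v_T | v_D | R | Approx. | Simulated |
|---|---|---|---|---|---|
| 80/50 | 0.16 | 0.25 | 1.25 | 9.0% | 8.0–8.5% |
| 90/50 | 0.09 | 0.25 | 1.62 | 15.7% | 14.2–14.5% |
| 95/50 | 0.0475 | 0.25 | 2.03 | 22.9% | 20.6–20.7% |
| 90/30 | 0.09 | 0.21 | 1.50 | 13.6% | 12.5% |
| 90/20 | 0.09 | 0.16 | 1.33 | 10.4% | 9.2–9.8% |
| 90/10 (documented) | 0.09 | 0.09 | 1.00 | 5.0% | 4.7–5.3% |
| 60/10 | 0.24 | 0.09 | 0.63 | 0.9% | about 1% |
| 50/10 | 0.25 | 0.09 | 0.62 | 0.8% | 1.1% |

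The formula and the simulations agree on direction and rough size. A Greenhouse-Geisser correction barely changes the result (14.4% to 14.2% at 90/50, and 1.1% both ways at 50/10), because the fault is unequal variance between arms, not lack of sphericity.

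**4. Does the choice of test matter?** Rejection rates from 3,000 simulated trials each, correlation 0.5, assumed rates:

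| Scenario (D versus T) | ANOVA group | ANOVA group by time | Chi-squared at T2 | Any of three chi-squared |
|---|---|---|---|---|
| No effect, 30% at all times | 4.4% | 5.0% | 4.7% | 13.3% |
| Effect at T2 only, 30% versus 50% | 25% | 71% | 78% | 81% |
| Constant, 30% versus 45% | 80% | 4% | 57% | 84% |

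For three independent tests the any-of-three figure would be 1 − 0.95³ = 14.3%. At 90% versus 10% at every time, the group effect and the chi-squared tests all have power of about 1.00.

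**The case against.** The strongest reply is that the sentence beside the primary endpoint is specific and the analysis section is a generic list that also serves side effects and baseline data. On that reading the ANOVA governs, and its term and contrast can wait for a statistical analysis plan. This would remove the duplication. It would still leave a method for continuous data on a yes/no endpoint, and a later plan would have to overrule a stated method, not fill a gap. The ANOVA may have been meant for the 0–10 pain scores, but the text does not say so.

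Several stronger readings are tempting, and the documents do not support them.

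- *The ANOVA inflates the error rate of the efficacy test.* No section makes group by time the efficacy test. For a claim of analgesic efficacy the group main effect is the natural term, and it keeps its size.
- *The smaller control arm will usually have the larger variance.* At the documented 90% and 10% the variances are equal. With control at 10%, any treatment rate between 10% and 90% gives control the smaller variance, and the test is then conservative. Inflation needs control relief nearer 50% than treatment relief. That is possible, since controls also receive oral morphine, but no documented rate shows it.
- *Complete-case deletion will cost a sizeable share of patients.* The documents give no rate of missed assessments, and all assessments fall within one episode in hospitalized patients.
- *The sample size is wrong as a result.* The 240 was set on regulatory grounds, and the planned effect would be detected by any of the candidate group comparisons.

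**Conclusion.** The point holds in a limited form. The article attaches an ill-suited method to its primary endpoint, gives another method for the same kind of data elsewhere, and sizes the trial on the latter. That is a conflict in stated text.

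The numerical consequence is conditional. The group main effect is sound in size. The group-by-time test can err in either direction, from about 1% to about 21% over the rates examined, and is correct at the documented 90/10. These figures assume a difference constant over time and a latent correlation of 0.5, and every pair of rates except 90/10 is an assumption. At the planning effect the ambiguity would not change the group comparison. It could if the true effect is smaller or differs between T1, T2 and T3.

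**What to change.** State one primary analysis of the binary endpoint, A+B+C pooled (n = 180) versus D (n = 60), in one of two ways:

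1. relief at T2, the time used for sizing, by chi-squared test with risk difference and 95% confidence interval, with T1 and T3 secondary; or
2. if all three times stay primary, a binomial GEE with logit link and robust standard errors, with a named contrast or a stated multiplicity rule.

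Describe the course of relief over T1, T2 and T3 with the GEE or a mixed logistic model. Keep repeated-measures linear models for the 0–10 pain score. Make Primary endpoint measures and Data management and analysis agree.

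The cost is wording only, with no new patients or data. The one real trade-off is that the first option takes primary status away from T1 and T3.

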#### Secondary endpoint measures

Secondary outcome measures will include treatment safety, adverse events, and satisfaction from both health professionals and patients. The total time of nitrous oxide/oxygen mixture administration will be also recorded.

### Sample size determination

According to our previous study on burn-dressing pain [17, 37], we used preliminary observational data obtained in medical oncology for 20 patients. We found that 90% of patients receiving pre-prepared nitrous oxide/oxygen mixture experienced pain relief (a decrease of at least 30% in pain intensity [47]) at 15 min versus 10% of patients in the control group. The aim of this study is to assess the efficacy of the nitrous oxide/oxygen mixture, so a sample size of 12 was targeted with a two-tail test with type-1 error rate of 0.05 and a power of 90% to be sufficient. We decided on a sample size of 240 to meet the Chinese Food and Drug Administration standard for feasibility and the safety of nursing staff in implementing this analgesic [17].

### Data management and analysis

Before the study, all data collectors will be trained in the data collection procedure. Data from withdrawn patients will not be used in the final analysis. SPSS version 22.0 (SPSS Inc., IBM Company, Chicago, IL, USA) will be used to conduct quantitative analysis following the intention-to-treat principle for a case-control randomized trial. Descriptive statistics will be analyzed by medians (inter-quartile ranges), means (standard deviations), and proportions (exact binomial 95% confidence intervals), as appropriate. Proportions will be compared by using the chi squared test or the Fisher’s exact test. Means will be compared using Student’s *t* test (normal distribution parameters) or a nonparametric two-sample Mann–Whitney test (non-normal distribution parameters). Statistical significance will be considered for *P* < 0.05.

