### Randomization, allocation concealment, and binding

Owing to the severity of the pain, ethicists suggest helping as many suffering patients as possible. In total, 240 participants will be randomized into four groups in a ratio of 3:1; three treatment groups (A, B, C), *n* = 180, and one control group (D), *n* = 60. The allocation sequence of each patient is decided by a computer-generated schedule, which is numbered by a statistician. The randomization schedule will be kept and sealed in an independent research room. Apart from the project manager, who is responsible for gas distribution, no other nurses or data collectors will have access to the data allocation. The nurse is blind to the double-blind randomized controlled trial lists (see Additional file 3) because the list does not indicate what treatment letters A, B, C, and D stand for.

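### Withdrawn patients are excluded from the final analysis while the next sentence claims intention-to-treat; the two rules conflict, and the exclusion can bias the primary comparison in either direction

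*Protocol article*

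**What the plan says.** Two adjacent sentences under Data management and analysis set the rules. The first is "Data from withdrawn patients will not be used in the final analysis". The second says that SPSS "will be used to conduct quantitative analysis following the intention-to-treat principle for a case-control randomized trial". (The case-control label is a separate slip and plays no part here.)

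The article does not define withdrawal, give an expected rate or reasons, or name a separate completer or per-protocol set to which the exclusion could apply.

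The rule acts on the primary endpoint: "The primary endpoint measures will be the percentage of patients receiving pain relief at T1, T2, and T3". The groups are "three treatment groups (A, B, C), *n* = 180, and one control group (D), *n* = 60". Table 1 places allocation at enrolment, before the treated episode. Under Treatments, the patient holds the mask, and gas continues until the episode ends.

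**The concern.** Intention-to-treat keeps randomised patients in the arm to which they were assigned. Removing some of them because of an event after randomisation gives a completers analysis. An analyst cannot do both, and may end up choosing between the rules after seeing the data.

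The endpoint is a percentage of patients, so each exclusion changes its denominator. Withdrawal could plausibly depend on arm or outcome. Under Measurement, the article lists nausea, vomiting, dizziness, drowsiness and headache as possible effects of the gas mixture. The sample-size section expects lack of relief to be far more common in the control arm. Side effects would push withdrawal towards the gas arms and lack of relief towards control. Either way, the groups compared would no longer be the groups randomised. The exclusion sentence makes no exception for safety data.

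**Working it through.** **The plan's own figure.** The only related calculation is the sample size: 90% versus 10% relief, two-sided alpha 0.05, power 90%, total 12. With equal arms and no continuity correction:

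n per arm = [1.96·√(2·0.5·0.5) + 1.2816·√(0.9·0.1 + 0.1·0.9)]² / 0.8² = (1.386 + 0.544)² / 0.64 ≈ 5.8, so 6 per arm and 12 in total.

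The figure reproduces. It contains no allowance for withdrawal, and the present point does not depend on it.

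**Inputs.** From the article: 180 gas and 60 control patients. Assumed, because the article gives no figures: true relief p equal in both arms at 50%, 60% or 70% (withdrawals counted as no relief); a fraction w of an arm withdraws; all who withdraw are non-responders.

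**Effect on an arm.** Completer relief rate = p / (1 − w). With p = 50%, it is 0.50/0.90 = 55.6% at w = 10% and 0.50/0.80 = 62.5% at w = 20%.

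**Effect on the test.** Let a and b be the completer rates, m₁ and m₂ the remaining numbers, d = a − b, SE₀ the pooled standard error and SE₁ the unpooled one. Then

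rejection probability = Φ((d − 1.96·SE₀)/SE₁) + Φ((−d − 1.96·SE₀)/SE₁).

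Example: p = 50%, 10% of the gas arms lost. m₁ = 162, m₂ = 60, d = 0.0556. Pooled rate = (90 + 30)/222 = 0.5405, SE₀ = 0.0753, SE₁ = 0.0754. Result: Φ(−1.22) + Φ(−2.69) ≈ 0.115 instead of 0.05.

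| True relief, both arms | Arm losing 10% | Gas completers | Control completers | Difference (points) | Rejection probability |
|---|---|---|---|---|---|
| 50% | gas | 55.6% | 50.0% | +5.6 | 11% |
| 50% | control | 50.0% | 55.6% | −5.6 | 11% |
| 60% | gas | 66.7% | 60.0% | +6.7 | 16% |
| 60% | control | 60.0% | 66.7% | −6.7 | 14% |
| 70% | gas | 77.8% | 70.0% | +7.8 | 23% |
| 70% | control | 70.0% | 77.8% | −7.8 | 19% |

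Simulating the same cases with exactly 18 gas patients (10% of 180) or 6 control patients (10% of 60) removed gives the same shifts and rejection rates of 12% to 25%.

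**Other patterns at 50% true relief.** Withdrawal of 20% (gas) and 5% (control) gives 62.5% − 52.6% = +9.9 points. The reverse split gives −9.9 points. With 10% in each arm the shift is 0.

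**With a real effect of 60% versus 40%.** Even balanced 10% withdrawal moves the difference from 20 to 66.7 − 44.4 = 22.2 points. A 20%/5% split gives 32.9 points and a 5%/20% split gives 13.2.

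**The case against.** **Condensed article.** A journal article leaves detail to an analysis plan that is not shown. That does not help here: the article itself states both rules, and any plan would have to break one of them.

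**Upward bias.** A reader might infer that the exclusion inflates the efficacy of the gas. The article gives no reasons for withdrawal and no split by arm. If control patients leave more often for lack of relief, the bias runs the other way. Only a bias of unknown sign is supported.

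**Mask removal.** A reader might also infer that anyone who takes the mask off early is withdrawn. The article does not say so. Self-administration is part of the intervention, duration of use is recorded, and T3 is timed from the end of gas, so it can be measured after early stopping. The term could mean withdrawn consent, or leaving before any treated episode.

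**Safety.** That adverse events of withdrawn patients would be lost depends on reading the final analysis to include safety. The article says side effects are monitored once inhalation starts and does not say such data are discarded.

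**Size.** This objection has force. The only documented relief rates are 90% versus 10%. At those rates, dropping every gas-arm non-responder moves 90% to 100%, against an expected difference of 80 points, and the conclusion would not change. The study also follows one short inpatient episode, so 10% withdrawal confined to one arm is a stress case. However, the documented rates come from preliminary data on 20 patients, and the Discussion cites a study of inhaled nitrous oxide in cancer-related incident pain with a non-significant reduction in pain scores. A smaller true effect is therefore worth guarding against.

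**Conclusion.** The contradiction is certain from the text and needs correcting: the article fixes an exclusion that its stated analysis principle forbids, and the exclusion changes the denominator of the primary endpoint.

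The consequence is conditional. Bias can go either way, depending on which arm loses more non-responders. The shift of about 6 to 8 points and the type I error of roughly 11% to 25% rest on assumed equal relief of 50% to 70% and on 10% withdrawal, all non-responders and all from one arm. They show what the rule permits and are not a forecast. At the article's own 90% versus 10%, the trial's conclusion would survive. Understated adverse events are a risk only if the exclusion extends to safety.

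**What to change.** - Delete the exclusion sentence.
- Analyse all randomised patients with a started study episode in the arm assigned. Because allocation precedes the episode, limit exclusion to patients who never have a treated episode, decided blind to arm.
- Keep collecting T1, T2 and T3 at their scheduled times after gas is stopped.
- Count a score missing because of withdrawal as no relief, at T1, T2 and T3 alike. Do not score as a failure a patient whose episode ended with relief before the assessment. Gas runs only until the episode is over, so a blanket rule that missing means failure could penalise fast responders. Add a sensitivity analysis for missing scores.
- Keep all exposed patients in the safety analysis, and label any completers analysis as secondary.

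The cost is a change of wording and continued scoring after gas stops. The calculated 12 and the planned 240 do not change. The downside is that relief rates may look slightly lower.

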## Methods

### Study design

This study is a randomized, double-blind, placebo-controlled, parallel clinical trial to test the analgesic efficacy of a fixed inhaled nitrous oxide/oxygen mixture on adult cancer patients with breakthrough pain. This article has been drafted following SPIRIT guidelines [43] (see Additional file 1). Patients in the treatment groups will receive standard pain treatment plus pre-prepared nitrous oxide/oxygen mixture and patients in the control group will receive standard pain treatment plus oxygen when they report a breakthrough pain episode. The study protocol will use the Consolidated Standards of Reporting Trials (CONSORT) [44] statement recommendations (see Additional file 2). The overall trial design is provided in Fig. 1. Furthermore, the schedule of enrolment, interventions, and assessments are presented in Table 1. The stratification factors were not contemplated in this study. breakthrough pain is a transitory exacerbation of pain that occurs despite the use of long-term and around-the-clock analgesics to control persistent pain, and there is no nature differences in two types of breakthrough pain. So we did not make stratification analyses in this study.

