### Measurement

Patient’s demographic data (age, sex, nationality, height, weight), cancer diagnosis, baseline breakthrough pain intensity, current background pain opioid medication dosage, duration of nitrous oxide/oxygen mixture use, dosage of oral rescue morphine medication, and any side or adverse effects of nitrous oxide/oxygen mixture treatment will be recorded by researchers [45]. A numerical pain rating scale (range from 0 to 10) is used to assess for pain intensity along with heart rate, noninvasive monitoring of blood pressure, and digitally monitored oxygen saturation at baseline (T0 before treatment), 5 min (T1) and 15 min (T2) after the beginning of treatment, and at 5 min (T3) after treatment finished. Heart rate, blood pressure, and oxygen saturation will be monitored by Infinity® Delta XL (Draeger Medial Systems Inc., Danvers, Shanghai, China). A five-point satisfaction scale (5, very satisfied; 4, satisfied; 3, uncertain; 2, dissatisfied; 1, very dissatisfied) will be used to assess both patients’ and healthcare professionals’ satisfaction with breakthrough pain treatment [46]. Any side effects of the nitrous oxide/oxygen mixture treatment, such as nausea, vomiting, dizziness, drowsiness, and headache [17], will be carefully monitored by researchers after the initiation of the gases inhalation.

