## Discussion

Many studies on transmucosal fentanyl showed excellent breakthrough pain reduction after 15 min administration [11, 23, 30, 48]. But that means patients have to suffer for at least 15 minutes severe pain. Furthermore, this fentanyl preparation is unavailable in China. In addition to the incompliance and adverse effects of oral immediate-release morphine, many other opioid formulations also appeared incapable of effectively relieving breakthrough pain due to their slow onset of actions (15–60 minutes) [11, 23, 30, 48]. This study intends to find a better alternative rescue medication for cancer patients with breakthrough pain in China.

The study of Li et al. on burns-dressing procedure pain showed faster pain reduction, within 15–20 s, for the pre-prepared nitrous oxide/oxygen mixture group [17, 37]. However, another study found that inhaled nitrous oxide showed a non-significant reduction in pain scores in metastatic dying patients with cancer-related incident pain [49]. In this study, we will attempt to verify both the analgesic efficacy of the fixed nitrous oxide/oxygen mixture, and patients’ and healthcare workers’ satisfaction in using the nitrous oxide/oxygen mixture for breakthrough pain management.

To our knowledge, this study is the first randomized controlled trial to evaluate the effectiveness of the pre-prepared nitrous oxide/oxygen mixture to treat breakthrough pain in cancer patients with advanced disease. If this treatment appears beneficial, this study can help to generate preliminary guidelines on breakthrough pain management in cancer patients with advanced disease. We intend to disseminate the results of this study to international journals and conferences.

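### The named tests do not use the T0 pain score as a covariate, a valid but less precise choice, and the reason given for not analysing by pain type conflicts with the protocol's own text.

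*Protocol article*

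**What the plan says.** **Tests.** In Data management and analysis, "Proportions will be compared by using the chi squared test" or Fisher's exact test; means go to a t test or Mann–Whitney test. Under Primary endpoint measures, repeated-measures ANOVA is named for the percentage relieved at T1, T2 and T3. No covariate is mentioned in either place.

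**Baseline.** In Measurement, "A numerical pain rating scale (range from 0 to 10) is used to assess for pain intensity" at T0, T1, T2 and T3, and Table 1 schedules the T0 score for all patients. Sample size determination describes relief as "a decrease of at least 30% in pain intensity".

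**Pain type.** Study design sets aside stratification factors and stratified analysis on the ground that "there is no nature differences in two types of breakthrough pain". The Background calls spontaneous pain unpredictable and incidental pain somewhat predictable with three sub-types, and puts more than half of breakthrough pain in the spontaneous class. The Discussion cites an earlier study in which inhaled nitrous oxide gave a "non-significant reduction in pain scores in metastatic dying patients with cancer-related incident pain". The variables listed in Measurement do not include pain type.

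**The concern.** A baseline measurement of the outcome is usually the best single predictor of the later value. It is already collected here, so using it as a covariate costs almost nothing. With only 60 controls the standard error is driven by the small arm, and any free reduction is worth having. The T0 score can also affect how easily a patient meets the 30% criterion, so it may carry information about the binary outcome even though it is the denominator of that outcome.

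Pain type is a separate matter. The only cancer-pain result for this gas that the Discussion cites was non-significant, and it was in incident pain. The plan then declines to look at type because the types do not differ. The Discussion hopes the trial will support preliminary guidelines for breakthrough pain, so readers will ask whether the result covers incident pain. If type is not recorded at the episode, it may not be recoverable later.

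**Working it through.** **1. The protocol's own figure.** Sample size determination uses a "two-tail test with type-1 error rate of 0.05 and a power of 90"%, with relief of 90% vs 10%. With pooled variance, 1:1 allocation and no continuity correction:

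n per arm = [1.96·√(2·0.5·0.5) + 1.2816·√(0.09 + 0.09)]² / 0.8² = (1.386 + 0.544)² / 0.64 = 5.8, so 6 per arm and 12 in total. The stated 12 is reproduced.

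**2. Power at the planned 180 vs 60 on those rates.** Pooled rate = (60·0.1 + 180·0.9)/240 = 0.70. Null SE = √(0.21·(1/60 + 1/180)) = 0.068; alternative SE = √(0.09·(1/60 + 1/180)) = 0.045. (0.8 − 1.96·0.068)/0.045 is about 15, so power is about 100%. Adjustment cannot add to that.

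**3. Pain score.** The documents give no SD, difference or correlation. Assume SD 1.9 and a difference of 0.8 at T2.

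- Unadjusted SE = 1.9·√(1/180 + 1/60) = 1.9·0.1491 = 0.283.
- SE adjusted for T0 = 0.283·√(1 − r²), where r is the T0–T2 correlation.
- Power = Φ(0.8/SE − 1.96).

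| r | √(1 − r²) | SE | Power |
|---|---|---|---|
| unadjusted | 1 | 0.283 | 81% |
| 0.3 | 0.954 | 0.270 | 84% |
| 0.5 | 0.866 | 0.245 | 90% |
| 0.7 | 0.714 | 0.202 | 98% |

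The proportional fall in SE depends only on r, not on the assumed SD.

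**4. How T0 enters the relief criterion.** If scores are whole numbers, the fall needed is 0.3·T0 rounded up:

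- T0 = 4: 1.2, so 2 points, a 50% fall.
- T0 = 7: 2.1, so 3 points, a 43% fall.
- T0 = 10: 3 points, a 30% fall.

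In a simulation of controls (assumed T0 mean 6.5, SD 1.5), relief was 39% at T0 ≥ 7 and 21% at T0 ≤ 5 with r = 0.3, but 32% vs 29% with r = 0.5. The dependence can be real, and it weakens as T2 tracks T0 more closely, because the percentage criterion then already absorbs T0.

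**5. Binary relief.** Assume a smaller effect, 30% vs 50%. Pooled rate = (18 + 90)/240 = 0.45. Null SE = √(0.2475·0.02222) = 0.0742; alternative SE = √(0.21/60 + 0.25/180) = 0.0699. Power = Φ((0.2 − 1.96·0.0742)/0.0699) = Φ(0.78) = 78.3%. Multiplying both SEs by √(1 − R²), with R² assumed:

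- R² = 0.02: 79.1%
- R² = 0.05: 80.4%
- R² = 0.10: 82.5%
- R² = 0.20: 86.9%

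The last is probably optimistic. Simulating a baseline covariate at about these rates gave adjusted/unadjusted SE ratios of 0.996 (log-odds 0.3 per SD) and 0.935 (0.8 per SD). The stronger one corresponds to R² = 1 − 0.935² = 0.13. Simulations of the 30% criterion itself, under several assumed T0 distributions, gave gains of about 3 to 7 power points at r = 0.2–0.3 and about 0 to 3 at r = 0.5 and above. These levels depend on assumptions that the documents do not supply.

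**6. By type.** Assume 30–50% of patients have incident pain. Controls: 0.3·60 = 18 to 0.5·60 = 30; treated: 54 to 90. The widest 95% half-width is 1.96·√(0.25/n + 0.25/(3n)):

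- n = 18: 27 points
- n = 30: 21 points
- all 60 controls: 15 points

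Power for 30% vs 50% within incident pain would be 30–48%.

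**The case against.** **T0 is not ignored.** A reader might infer from the unadjusted tests that the baseline goes unused. The documents do not support that: T0 is the denominator of the relief criterion and may be a level of the repeated-measures ANOVA. What is missing is T0 as a covariate. Neither use replaces it. If the ANOVA compares scores as change from T0, then with equal SDs the SE is 0.283·√(2(1 − r)), which is 0.335, 0.283 and 0.219 at r = 0.3, 0.5 and 0.7. That is larger than the adjusted SE each time.

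**The unadjusted comparison is not biased.** A reader might also infer that chance imbalance in T0 or pain type distorts the estimate. Randomisation makes the chi-squared test valid, its standard error already allows for such imbalance, and the whole-number arithmetic applies to both arms. This part of the objection stands in full.

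**The gain may not matter.** On the protocol's rates it does not change power. Those rates come from preliminary observational data on 20 patients, however, so a smaller effect is possible.

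**Adjusted models can be left to an SAP.** That is fair for detail. But the protocol itself names the tests, and it states its decision on pain type together with the reason, so that decision is not an omission.

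**The pain-type conflict is limited.** The Background puts both types under one definition and separates them by trigger and predictability, not by response to analgesia. The cited study was in dying patients with metastatic disease, and a non-significant result does not show absence of effect. It would therefore be too strong to call the trial uninterpretable for incident pain.

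**Conclusion.** The point holds as an inexpensive improvement, not as a flaw that invalidates the analysis. The size differs by outcome.

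- **Pain scores:** adjusting for T0 cuts the standard error by about 5%, 13% or 29% at correlations of 0.3, 0.5 or 0.7. The correlations are assumed.
- **Binary relief, the primary endpoint:** the gain is small, roughly 0 to 7 power points if the true effect is well below the planning value, and nil for power at 90% vs 10%.

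The secondary point rests on the text alone. The stated reason for not analysing by type does not fit the protocol's own Background and Discussion. The overall comparison remains valid for the mix of patients enrolled, but as planned it cannot show whether the effect extends to incident pain.

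**What to change.** - Analyse relief at each planned time point (T1, T2, T3) by logistic regression on arm with the T0 pain score as covariate, reported as a standardised risk difference with its confidence interval.
- Compare pain scores by ANCOVA on T0 instead of the t test.
- Delete the statement in Study design that the two types do not differ in nature.
- Record pain type (spontaneous or incident) at T0, and report the effect by type descriptively with confidence intervals.

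The cost is wording in the analysis section and one case report form field, unless the full form already holds it. The by-type estimates will be imprecise, with about 18–30 incident-pain controls on the assumed share, and should be labelled as descriptive.
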